### Follow-Up

All patients with mild to moderate AD will undergo physical examinations, skin lesion assessments, and laboratory tests at baseline (day 0) and at week 4 after enrollment. Treatment efficacy will be evaluated during follow-up visits at weeks 1, 2, and 4. Detailed information on data collection, physical examinations, and skin lesion assessments is shown in Table 3.

**Table 3. T3:** Study schedule of Inflammation Formula Number 1 clinical trial (4 weeks).

Indicator	Baseline visit 1 (week 0)	Treatment visit 2 (week 1)	Treatment visit 3 (week 2)	Treatment visit 4 (week 4)
Informed consent	✓			
Demographic feature	✓			
History of surgical treatment	✓			
History of disease	✓			
Vital signs	✓	✓	✓	✓
Physical examination	✓	✓	✓	✓
Pregnancy test	✓			
Inclusion and exclusion criteria check	✓			
Randomization	✓			
EASI^a^	✓	✓	✓	✓
IGA^b^	✓	✓	✓	✓
DLQI^c^	✓	✓	✓	✓
BSA^d^	✓	✓	✓	✓
PNRS^e^	✓	✓	✓	✓
POEM^f^	✓	✓	✓	✓
TCM^g^ symptom scores	✓	✓	✓	✓
Laboratory examinations	✓			✓
Safety and medication information	✓			✓

a EASI: Eczema Area and Severity Index.

b IGA: Investigator Global Assessment.

c DLQI: Dermatology Life Quality Index.

d BSA: body surface area.

e PNRS: Pruritus Numeric Rating Scale.

f POEM: Patient-Oriented Eczema Measure.

g TCM: traditional Chinese medicine.

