### Interventions

In this study, patients in the traditional decoction group, the standard-dose granule group, the two-thirds dose granule group, and the one-tenth dose granule group will receive treatment twice daily, 30 minutes after breakfast and dinner, at a dose of 200 mL for 4 consecutive weeks. All patients will receive baseline therapy with desonide cream combined with urea ointment, applied twice daily for 14 days. After 14 days, desonide cream will be discontinued, and urea ointment will be continued alone for an additional 14 days. The detailed composition of IFN-1 is presented in Table 1, and the dosage of each herbal component in different formulations is shown in Table 2. The IFN-1 granules used in this study were manufactured by Guangdong Efang Pharmaceutical Co, Ltd in compliance with Good Manufacturing Practice. Quality control procedures included authentication of raw herbal materials, testing for heavy metals, pesticide residues, microbial contamination, and batch-to-batch consistency, following the standards of the Chinese Pharmacopoeia (2020 edition).

**Table 1. T1:** Detailed drug composition of Inflammation Formula Number 1 (IFN-1).

Chinese name	Latin name	Pharmacologic activity
Sheng Di Huang	*Rehmannia glutinosa*	Immunomodulation and anti-inflammatory
Dan Shen	*Salvia miltiorrhiza*	Microcirculation improvement and antioxidant
Fang Feng	*Saposhnikovia divaricata*	Antiallergic and analgesic
Da Qing Ye	*Isatis indigotica*	Anti-inflammatory and antiviral
Dang Gui	*Angelica sinensis*	Immunomodulatory and antithrombotic
Ku Shen	*Sophora flavescens*	Antipruritic and anti-inflammatory
Huang Qin	*Scutellaria baicalensis*	Antiallergic, antibacterial, and antifungal
Xia Ku Cao	*Prunella vulgaris*	Antioxidant and immunosuppressive
Bai Xian Pi	*Dictamnus dasycarpus*	Anti-inflammatory and antifungal
Gan Cao	*Glycyrrhiza uralensis*	Steroid-like activity and anti-inflammatory

**Table 2. T2:** Composition and dosage of Inflammation Formula Number 1 in different formulations.

Chinese name	Traditional decoction (g)	Standard-dose granule (g)	Two-thirds dose granule (g)	One-tenth dose granule (g)
Sheng Di Huang	15	15	10	1.5
Dan Shen	9	9	6	0.9
Fang Feng	6	6	4	0.6
Da Qing Ye	9	9	6	0.9
Dang Gui	9	9	6	0.9
Ku Shen	9	9	6	0.9
Huang Qin	9	9	6	0.9
Xia Ku Cao	9	9	6	0.9
Bai Xian Pi	9	9	6	0.9
Gan Cao	6	6	4	0.6

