### Safety Assessment

Before enrollment, all patients diagnosed with mild to moderate AD will undergo a standardized informed consent process, during which comprehensive information regarding the study objectives, potential benefits, and possible risks will be fully disclosed. An adverse event is defined as any unfavorable medical occurrence after treatment, including symptoms, signs, diagnosable diseases, or abnormalities in laboratory test results, regardless of whether a causal relationship with the study intervention is established. Participants will report all adverse events occurring during the 4-week treatment period. All reported events will be documented in case report forms (CRFs), together with precise timing and detailed clinical descriptions.

In accordance with clinical practice guidelines, any patients who experience a serious adverse event will be immediately withdrawn from the study and provided with free medical management as specified in the study protocol. These safety measures are designed to ensure rigorous data collection and safeguard participant well-being throughout the trial. Given the minimal risk associated with this study, an independent data monitoring committee will not be established.

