### Data Collection and Management

This study will adopt a standardized data collection and management procedure. All study data will be collected using CRFs completed by dermatologists who have received unified training. The CRFs consist of six sections: (1) demographic characteristics, including age, sex, date of birth, marital status, and so forth; (2) medical history, including disease history, prior surgical treatments, allergy history, and family history of AD; (3) vital signs and physical examination, including height, weight, and BMI; (4) disease severity and treatment efficacy assessments, conducted at baseline (week 0), week 1, week 2, and week 4, including the EASI, IGA, DLQI, BSA, PNRS, POEM, and TCM syndrome scores; (5) laboratory examinations, including pregnancy testing, routine blood tests, routine urinalysis, and assessments of liver and renal function; and (6) safety and medication information, including prior medication use, concomitant medications, and adverse events.

In this study, a database will be established using EpiData (version 3.1; EpiData Association), with input validation rules defined for each variable, including data type, value ranges, and logical checks. Data entry will be performed independently using a double-entry method, followed by consistency checks between the 2 datasets. Any discrepancies will be resolved by referring to the original CRFs until complete agreement is achieved. The finalized database will be converted into SAS datasets, and data validation and logical checks will be conducted using SAS (version 9.4; SAS Institute) [18].

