### Statistical Analysis

Statistical analyses will be performed using SAS (version 9.4). The primary analysis will follow the per-protocol principle, with supportive analyses conducted under the intention-to-treat framework including all randomized patients. Missing data will be handled under the missing-at-random assumption using sequential regression multiple imputation. This study is designed as an equivalence trial, with the primary end point being the proportion of patients achieving EASI50 at week 4. The prespecified equivalence margin (Δ) was set at 15% based on clinical considerations. Equivalence will be assessed using the 2-sided 95% CI approach: the difference in EASI50 response rates between groups will be estimated, and the corresponding 95% CI will be constructed using the chi-square test. Equivalence will be concluded if and only if the entire CI lies within the predefined margin of −15% to +15%. For intergroup comparisons among the 4 treatment groups, an overall test will first be performed. Subsequently, pairwise comparisons will be conducted where appropriate. Between-group comparisons will be performed using the Student *t* test (2-tailed) or Wilcoxon rank-sum test, as appropriate. For multiple pairwise comparisons, Bonferroni correction will be applied to control for type I error. Linear mixed-effects models will be applied for continuous outcomes, and generalized linear mixed models will be used for binary outcomes, with subject-specific random effects to account for within-subject correlation and to appropriately handle missing data. Categorical variables will be expressed as frequencies and percentages and compared using the chi-square test or Fisher exact test. In addition, a dose-response model will be constructed to characterize the dose-response relationship of granules and to explore the formulation conversion between granules and traditional decoction. Except for the equivalence testing described above, a 2-sided *P*<.05 will be considered statistically significant.

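### Table 3 schedules the adverse event and concomitant medication record only at baseline and week 4, leaving a 28-day gap in which non-serious events and added medication may rest on recall

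*Protocol article*

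**What the plan says.** Table 3, under Follow-Up, has a row named "Safety and medication information". It is ticked at week 0 and week 4, and the cells for weeks 1 and 2 are empty. Data Collection and Management gives the content of that section of the case report form: "safety and medication information, including prior medication use, concomitant medications, and adverse events".

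Patients attend between those two points. Follow-Up states: "Treatment efficacy will be evaluated during follow-up visits at weeks 1, 2, and 4". At weeks 1 and 2, Table 3 ticks vital signs, physical examination and all seven efficacy and patient-reported scales.

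Safety Assessment sets the standard for the safety data: "Participants will report all adverse events occurring during the 4-week treatment period", and "All reported events will be documented in case report forms (CRFs), together with precise timing and detailed clinical descriptions". It names no visit, diary or contact at which patients are asked. For serious events it adds that "any patients who experience a serious adverse event will be immediately withdrawn from the study".

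**The concern.** The schedule is sparser than the safety text needs. If non-serious events and extra medication are asked about systematically only at week 4, a patient has to date and describe something that may have happened almost four weeks earlier.

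Four features of this trial make that matter:

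- Safety is a stated aim, alongside efficacy and dose-response. It is to be compared across a decoction and three granule doses.
- Treatment is open-label for patients and investigators, so what is remembered and reported could differ with the known dose.
- Background topical treatment changes halfway: "After 14 days, desonide cream will be discontinued, and urea ointment will be continued alone for an additional 14 days". A single week 4 record covers both halves. Events or added topical products before and after the change would have to be separated from memory, and products added late could affect EASI50 at week 4.
- Statistical Analysis says: "The primary analysis will follow the per-protocol principle". The medication record may bear on who belongs in that set.

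**Working it through.** The article gives no figure to reproduce, and the point depends on no sample size, power or error rate. The check compares the sections and counts days.

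**Step 1. Are the empty cells real?** The laboratory row of Table 3 has the same pattern, with ticks at baseline and week 4 only. The text under Follow-Up confirms that timing for laboratory tests. The pattern is therefore unlikely to come from the conversion of the table.

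**Step 2. Does the row cover adverse events and concomitant medication?** Yes. Data Collection and Management lists both in the section of that name. It gives visit times for the disease severity and efficacy section but none for the safety and medication section, so Table 3 is the only place where its timing is fixed.

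**Step 3. Is collection at weeks 1 and 2 scheduled elsewhere?** No. Safety Assessment defines the reporting period and the detail required, but no time of asking. Withdrawal and Dropout provides for recording the reasons for withdrawal, but no closing safety record.

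**Step 4. Count the gaps.** Taking visits on their nominal days (0, 7, 14 and 28; the article gives no visit windows):

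| Row ticked at | Gaps between scheduled records (days) | Longest gap | On-treatment visits with the record |
|---|---|---|---|
| Weeks 0 and 4 (Table 3 as it stands) | 28 − 0 = 28 | 28 | 1 of 3 |
| Weeks 0, 1, 2 and 4 | 7 − 0 = 7; 14 − 7 = 7; 28 − 14 = 14 | 14 | 3 of 3 |

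**Step 5. Relate the gap to the change in background treatment.** Desonide stops after 14 days. The single 28-day interval therefore mixes 14 days with desonide and 28 − 14 = 14 days without it. A record at the week 2 visit, nominally day 14, would separate the two periods.

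**The case against.** The strongest reply is that Table 3 shows when a form section is scheduled, not the only time at which events are captured. Safety Assessment has participants reporting over the whole treatment period, and immediate withdrawal after a serious event could not work if events surfaced only at week 4. How events are elicited between visits is also detail that an article may leave to the full protocol. This stands to the extent that reliance on recall is a possibility and not a stated feature of the plan. The 28 days are a gap between scheduled records, not a demonstrated recall window. The reply does not remove the point, because the article prints an explicit visit schedule that omits this record at two attended visits. That is something stated, not detail left out.

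Three stronger readings are tempting, and the article supports none of them:

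- **That weeks 1 and 2 yield no safety data.** Table 3 ticks vital signs and physical examination at both visits, and the definition of an adverse event includes signs, so these checks can reveal events. (The sentence under Follow-Up names physical examination only at baseline and week 4, but the table ticks it at every visit.)
- **That patients who leave early contribute no safety information.** Reported events go into the case report form whether or not the patient completes treatment, and reasons for withdrawal are recorded.
- **That the planned 5% dropout implies 5% × 300 = 15 patients without on-treatment safety data.** The 5% is an allowance in the sample size calculation for the equivalence comparison. Turning it into a count of missing safety records needs the previous reading to be true.

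The link to the primary analysis is also indirect. The article does not define the per-protocol set or say that concomitant medication decides membership, and medication recorded at week 4 can cover the whole period.

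**Conclusion.** The point holds in a limited form. Table 3 gives non-serious adverse events and concomitant medication one systematic record after baseline, at 1 of 3 attended on-treatment visits and after a 28-day gap. That fits poorly with the precise timing asked for in Safety Assessment, and the two sections should be reconciled. The likely effect is less accurate dating and less complete capture of mild events and added medication, most plausibly around the desonide stop. The size of that effect cannot be calculated from the document.

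The conclusion assumes that the printed ticks reflect the intended schedule and that no between-visit questioning is planned in documents not shown. If such questioning is planned, what remains is a correction to the table. The EASI50 estimate and the equivalence test are not directly affected. The point is worth settling before recruitment because the change is cheap, whereas undated or forgotten events cannot be reliably recovered afterwards.

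**What to change.** In Table 3, tick the safety and medication row at weeks 1 and 2 as well as at baseline and week 4. Add a note that the section is also completed at the last contact for any patient who withdraws early. The schedule then agrees with Safety Assessment. If ongoing collection between visits is already intended, state it in the table.

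The cost is one page of the case report form and a few minutes at each of two existing visits, plus that page at the last contact of an early withdrawal. No visit is added, and sample size and analysis stay the same. The abstract reports that no patient had been recruited at submission, so the change can be made before any data are collected.

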### Outcomes

#### Primary Outcome

The primary outcome indicator of this study is the proportion of patients achieving EASI50 after 4 weeks of treatment.

The EASI is used to assess the extent and severity of AD. Four body regions are evaluated separately: head and neck, upper extremities, trunk, and lower extremities. For each region, the percentage of affected area is scored on a 7-point scale (0‐6): 0 (0%), 1 (<10%), 2 (10%‐19%), 3 (20%‐49%), 4 (50%‐69%), 5 (70%‐89%), and 6 (90%‐100%). In each region, 4 clinical signs—erythema, edema or papulation, excoriation, and lichenification—are each graded on a 4-point severity scale (0‐3: none, mild, moderate, or severe). The sum of the 4 signs is multiplied by the area score and a region-specific weighting factor reflecting body surface distribution: head and neck (0.1), upper limbs (0.2), trunk (0.3), and lower limbs (0.4). The total EASI score is obtained by summing all 4 regional scores, ranging from 0 to 72, with higher scores indicating more severe disease. On the basis of the EASI score, the skin lesion condition of patients with AD is categorized as mild (0‐7 points), moderate (7‐21 points), or severe (>21 points). EASI is a static assessment completed independently at each visit. Consistent scoring by the same investigator and proper training ensure accuracy and reliability.

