### Inclusion Criteria

The inclusion criteria for patients with mild to moderate AD are as follows: (1) aged 18 to 60 years, regardless of sex; (2) a clinical diagnosis meeting the Williams diagnostic criteria for AD, with an Eczema Area and Severity Index (EASI) score ≤21 and body surface area (BSA) involvement between 3% and 20%; (3) meeting the TCM diagnostic criteria for wind-damp-heat stagnation syndrome (red, swollen skin with severe burning pruritus, oozing and yellow crusting due to scratching, often accompanied by dry mouth, dark urine, a red tongue with yellow greasy coating, and a slippery-rapid or wiry-rapid pulse; the condition recurs and worsens in hot, humid environments); (4) Investigator Global Assessment (IGA) score ≥3; and (5) provision of written informed consent [12].

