### Sample Size

This study is designed as an equivalence clinical trial to compare the traditional decoction and the standard-dose granule of IFN-1, with the primary outcome being the proportion of patients with mild to moderate AD achieving EASI50 after 4 weeks of treatment. EASI50 is defined as the percentage of patients achieving ≥50% improvement in EASI score from baseline, reflecting the treatment’s effectiveness in skin lesion improvement. On the basis of previous studies, the EASI50 rate is expected to be 90% in both the traditional decoction group and the granule group at the standard dose. Setting the equivalence margin at Δ=15%, α=.05 (2-sided), and β=.20, the required sample sizes under a 2:1 allocation are 94 and 47, respectively. Considering a 5% dropout rate, the sample sizes are increased to 100 and 50 for the decoction group and the granule standard-dose group, respectively. To explore the dose-response relationship, we include a two-thirds dose granule group (n=50) and a one-tenth dose granule group (n=50). Additionally, 50 patients are added to the standard-dose granule group to strengthen the robustness of the findings. The final study therefore uses a 4-arm parallel design with an allocation ratio of 2:2:1:1 into traditional decoction (n=100), standard-dose granule (n=100), two-thirds dose granule (n=50), and one-tenth dose granule (n=50).

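### The printed EASI area bands are irregular at the cut between scores 2 and 3 (20%), probably a transcription slip; check them against the instrument form before recruitment

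*Protocol article*

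**What the plan says.** The Primary Outcome section states the EASI scoring rule explicitly. On area it says "For each region, the percentage of affected area is scored on a 7-point scale", from 0 to 6. The bands are 0% (score 0), below 10% (1), then "2 (10%‐19%), 3 (20%‐49%), 4 (50%‐69"%), followed by 70-89% (5) and 90-100% (6).

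The rest of the rule is: "The sum of the 4 signs is multiplied by the area score and a region-specific weighting factor reflecting body surface distribution". The weights are "head and neck (0.1), upper limbs (0.2), trunk (0.3), and lower limbs (0.4"), and the total is described as "ranging from 0 to 72, with higher scores indicating more severe disease".

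This score feeds several parts of the plan:

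- **Primary endpoint.** Under Sample Size, "EASI50 is defined as the percentage of patients achieving ≥50% improvement in EASI score from baseline".
- **Secondary endpoints.** EASI75 and EASI90 use the same score (Secondary Outcomes).
- **Entry.** Inclusion Criteria requires a diagnosis "with an Eczema Area and Severity Index (EASI) score ≤21 and body surface area (BSA) involvement between 3% and 20"%.

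The article gives no other set of area bands. It does not say that the instrument has been modified.

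**The concern.** One band stands out. Score 3 covers about 30 percentage points and its lower neighbour, score 2, covers about 10. The bands above score 3 follow an even 20, 20, 10 pattern. Moving a single cut-point makes the whole sequence symmetric, which is what one would expect if a digit had been miscopied in two adjacent bands.

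The cut lies in a range that can matter here. With total involvement of 3% to 20% of body surface, a single region can readily reach 20-29%. If the printed cut is a slip and assessors at the five centres follow it, those regions get a higher area score than the instrument intends, and responder status on the primary endpoint can change. If some centres follow the printed text and others a form with a different cut, the scale also differs between centres.

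**Working it through.** **Inputs.** Area bands, sign grades (four signs, each 0-3), weights and total range come from Primary Outcome. Entry limits come from Inclusion Criteria. The comparison cut of 30% is an assumption: it is inferred from the regularity of the other bands and appears nowhere in the documents.

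**1. The plan's own figure.** Maximum EASI = (4 × 3) × 6 × (0.1 + 0.2 + 0.3 + 0.4) = 12 × 6 × 1.0 = 72, as stated. The maximum uses only the top band, so it holds for either cut and cannot tell them apart.

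**2. Band widths (approximate, in points).**

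| Score | 1 | 2 | 3 | 4 | 5 | 6 |
|---|---|---|---|---|---|---|
| As printed | 10 | 10 | 30 | 20 | 20 | 10 |
| 2/3 cut at 30% | 10 | 20 | 20 | 20 | 20 | 10 |

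The printed bands have no gaps or overlaps in whole percentages.

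**3. Regional score.** At 20-29% involvement the area score is 3 as printed and 2 with the 30% cut. The ratio is 3/2 = 1.5 for any sign sum and weight. Elsewhere the two scales agree.

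**4. Responder status, one affected region.** The weight cancels in a percentage change, so the score is sign sum × area score.

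| Area change | Sign sum | As printed | 30% cut | Threshold crossed |
|---|---|---|---|---|
| 25% to 15% | 8 to 6 | 24 to 12, fall 50% | 16 to 12, fall 25% | EASI50 as printed only |
| 35% to 25% | 8 to 6 | 24 to 18, fall 25% | 24 to 12, fall 50% | EASI50 with 30% cut only |
| 25% to 5% | 8 to 6 | 24 to 6, fall 75% | 16 to 6, fall 62.5% | EASI75 as printed only |
| 35% to 25% | 8 to 3 | 24 to 9, fall 62.5% | 24 to 6, fall 75% | EASI75 with 30% cut only |
| 25% to 5% | 8 to 2 | 24 to 2, fall 91.7% | 16 to 2, fall 87.5% | EASI90 as printed only |
| 35% to 25% | 8 to 1 | 24 to 3, fall 87.5% | 24 to 2, fall 91.7% | EASI90 with 30% cut only |

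Status can change both ways at every threshold.

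**5. Entry limit, extreme case.** Put all four regions at 20%, so total involvement is at its 20% cap. With the same sign sum S in each region, EASI = 3S as printed and 2S with the 30% cut:

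- S = 7: 21 against 14, eligible under both.
- S = 8, 9, 10: 24, 27, 30 (above 21) against 16, 18, 20 (eligible).
- S = 11: 33 against 22, above 21 under both.

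Eligibility differs only for S from 8 to 10, even in this corner case.

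**6. Illustrative size.** The documents give no regional distributions, so two simulations with invented ones, both restricted to 3-20% involvement, show a range.

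- **First** (involvement uniform over 3-20%, spread at random over regions): about 38% of patients have a region at 20-29%. EASI50 status differs in 2.3% to 4.2%, and the EASI50 rate is 1.4 to 2.2 points higher as printed.
- **Second** (skewed regional areas, sign sums 4-10): about 32% have such a region. With high response, the rate is 83.4% as printed and 80.8% with the 30% cut; 2.9% of patients respond only as printed and 0.4% only with the 30% cut. With low response, the rates are 46.0% and 41.4%, with 5.9% and 1.2% changing. EASI exceeds 21 in about 0.1% as printed and almost never with the 30% cut.

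**The case against.** The strongest reply is that the documents hold no standard against which the printed bands are wrong. The bands are exhaustive, they reproduce the 0-72 range, and nothing requires an ordinal area score to have equal widths. Steep steps at a boundary prove nothing either: with a 30% cut, 29% to 10% would show no change and 30% to 29% would lose a third. All of this stands. It means that the slip is inferred, not demonstrated, and that the document does not contradict itself on this point. It does not explain why a named instrument should carry one triple-width band beside a single-width one, with no modification declared.

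A second reply is that one rule applies at every visit and in every arm. That also stands as the text is written. Randomization is stratified by hospital, so even a difference in scoring between centres would not load on one arm by design. The article also asks for trained assessors and the same scorer throughout, and the case report form is not shown, so the sites may never use the printed line.

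A reader might infer more than the text allows:

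- **That the scale is shown to be distorted, or that response is always inflated.** Both need reference bands, and individual changes go both ways. Only the net direction was upward, under invented distributions.
- **That the entry limit is seriously affected.** The check shows an effect close to nil.
- **That the 15% margin rests on earlier EASI50 rates and is undermined.** Statistical Analysis bases the margin on clinical considerations. Only the expected 90% rate is attributed to previous studies, and their area bands are not shown.

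**Conclusion.** The concern holds as a probable transcription slip in the scoring rule for the primary endpoint. The printed sequence is irregular at exactly one cut, and moving that cut to 30% makes the sequence symmetric.

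If it is a slip, regions with 20-29% involvement score 1.5 times higher than intended, and single-patient EASI50, EASI75 and EASI90 results can change in either direction. Across both simulations, EASI50 status changes in about 2% to 7% of patients, and the rate moves by about 1.4 to 4.7 points. These sizes rest on the assumed 30% cut and on invented distributions of area and severity, so they show an order of magnitude only.

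There is no built-in bias towards an arm, little effect on the EASI limit of 21, and no effect on the sample size calculation. The point deserves attention because it concerns an explicit rule for the primary endpoint and is easy to settle before the first patient is scored.

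**What to change.** Before recruitment:

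1. Check the printed bands against the EASI form on which the sites are trained and against the case report form.
2. If the slip is confirmed, correct the Primary Outcome text and the case report form so that score 2 is 10-29% and score 3 is 30-49%. If the printed bands are intended, say that they are a deliberate modification of the instrument and give the reason.
3. Record the percentage of each region affected, and derive the area score in the database. One rule then applies at all five centres. Scores can also be recalculated if a band proves wrong later, which is impossible if only the area score is kept.

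The cost is one line of protocol text, a check of the form and a short derivation in the database. No patients, visits or procedures are added.
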